### Recruitment

Eligible individuals should be in the pre-diabetic range of diabetes: fasting plasma glucose (FPG) 100–125 mg/dL, 2-h post-load plasma glucose (PG) 140–199 mg/dL, or HbA1c 5.7–6.4% (39-46 mmol/mol) [20]. The age and body mass index (BMI) criteria are set at 30 years and older and ≥23 kg/m^2^.

Exclusion criteria are as follows: 1) previous diagnosis of diabetes or diabetes treatment; 2) inability to adhere to lifestyle modification; 3) uncontrolled hypertension or significant ischemic heart disease requiring hospitalization within 6 months of enrollment; 4) either heart failure, anemia (WHO criteria), or cancer requiring treatment in the past 5 years or renal insufficiency; 5) severe liver dysfunction or alcohol abuse; 6) significant arthritis or psychiatric problems; 7) either pregnant or planning to become pregnant; 8) several medications (thiazide, beta blockers, steroid, immune-modulating agents, agents for weight reduction); and 9) other systemic illness affecting the performance of this intervention program.

The screening process is a two-step approach. If the examinees of a national health examination agree to provide their personal information, informed consent is obtained at the time of the health examination. The “healthcare manager” in healthcare centers in Chungju and Suwon city can gain access to the database consisting of the health examination results of the examinees of the habitable areas covered by the healthcare centers. The candidates of this study who are aged ≥30 years, with a BMI ≥ 23 kg/m^2^ are initially screened by fasting glucose level (100-125 mg/dL) from the NHIS database. The C-KDPS program is announced to candidates in both Chungju and Suwon city via brochure or telephone, banner exhibition in the public healthcare centers, and extensive advertisement through the healthcare centers’ web pages.

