After initial screening, the participants are instructed to visit their nearby public healthcare centers after overnight fasting. With the informed consent process, the subjects perform a 75-g oral glucose tolerance test (OGTT), HbA1c level, and questionnaires regarding lifestyle habits. Additional blood sampling is done at 30 and 120 min for PG, insulin, and C-peptide levels using the standardized manual of operations [21], and shipped to the central laboratory within 24 h of sample collection. The questionnaires contain self-reported personal data about medical history, employment, education, economic status, smoking or alcohol use, and lifestyle habits including diet and physical activity habits. If the glucose and HbA1c levels of subjects are within the pre-diabetic range, the subjects are recommended to participate in this C-KDPS. In addition, demographic data and a standard 12-lead electrocardiogram are obtained. Anthropometric and laboratory analysis are scheduled to be conducted at baseline, 6, 12, 18, and 22 months.

Recruitment of participants began on July 1, 2016. The enrollment of the participants is expected to be complete by the end of January 2017. Intervention and follow-up of study subjects will be ongoing until December 2018.

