### Study outcomes

The primary outcome is new development of diabetes diagnosed by 2016 ADA criteria. A 75-g OGTT with HbA1c level testing is scheduled at 6, 12, 18, and 22 months. Secondary outcomes consist of cardiovascular disease (CVD) risk factors, changes in demographic characteristics with pancreatic β-cell function, insulin sensitivity, lifestyle habits, quality of life, feasibility or compliance of bidirectional web-based program, and health costs for the C-KDPS.

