### Statistical analysis

The C-KDPS sample size was determined for the primary outcome (between-group difference in diabetes incidence) at 22 months’ follow-up with type 1 error(α) = 0.05 and power (1-β) ≥ 0.80. We aimed to detect a cumulative incidence difference of 11% between the two intervention groups (control group = 19.8% vs. intensive LSI group = 8.6%) based on previous studies [7, 9]. A total of 420 subjects should be recruited, considering the dropout rate of 25% during the study period.

The primary and secondary outcomes will be analyzed using the intention-to-treat approach. Differences in participants’ baseline characteristics and clinical outcomes between two groups were evaluated by a two-sample *t*-test for continuous outcomes and by a Chi-square test or Fisher’s exact test for categorical outcomes. A mixed-model analysis of covariance, including treatment group, gender, age, and the terms and baseline values of clinical parameters, will be used to assess the effects of intervention in a post-intervention survey. For the primary outcome—the comparison of cumulative incidence of diabetes between two groups—a log-rank test with random effects for intercept to account for pre-post correlations within individuals will be used. An interaction effect between time and intervention group will be assessed first. If there is no interaction effect, the overall intervention difference will be assessed. Otherwise, the intervention difference will be assessed at each time point. Adherence to the LSI program is measured by evaluating class attendance, weight loss goal at 6 months, maintenance of physical activity, and achievement of diet goal. For long-term effects of intervention, cost-effectiveness analysis will be analyzed using the Markov model [24].

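### The primary test is stated as a log-rank test with a random intercept and a time-by-group interaction step; a log-rank test has neither, so this wording cannot be carried out literally and one test should be named.

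*Protocol article*

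**What the plan says.** All quotes are from the protocol article.

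- **Endpoint** (Study outcomes): "The primary outcome is new development of diabetes diagnosed by 2016 ADA criteria".
- **Visits** (Study outcomes): "A 75-g OGTT with HbA1c level testing is scheduled at 6, 12, 18, and 22 months".
- **Status at entry** (Recruitment): people with "previous diagnosis of diabetes or diabetes treatment" are excluded. After the screening tests, "If the glucose and HbA1c levels of subjects are within the pre-diabetic range, the subjects are recommended to participate in this C-KDPS".
- **Primary contrast** (Statistical analysis): "the comparison of cumulative incidence of diabetes between two groups".
- **Primary test** (Statistical analysis): "a log-rank test with random effects for intercept to account for pre-post correlations within individuals will be used".
- **Next step** (Statistical analysis): "An interaction effect between time and intervention group will be assessed first". Without an interaction, the overall difference is tested. With one, the groups are compared visit by visit.
- **General sentence** (Statistical analysis): baseline characteristics and clinical outcomes are compared by a t-test if continuous and "by a Chi-square test or Fisher’s exact test for categorical outcomes".

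**The concern.** The sentence fixes the trial's main test, and its parts do not fit together. A random intercept for within-person pre-post correlation, followed by a time-by-group interaction, describes a mixed model for repeated continuous measurements. The sentence just before it sets out such a model, so the wording may have been carried over; that is an inference. It does not describe a log-rank test of a first event.

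An analyst therefore has to depart from the text somewhere. The options include a plain log-rank test, some mixed model of diabetes status at each visit, or up to four separate visit comparisons. The document does not say which of these gives the primary p-value, and it states no multiplicity control for the visit-by-visit route. A main analysis should not leave that open.

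**Working it through.** **1. Can the stated test be carried out literally?**

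- The log-rank statistic sums observed minus expected events over risk sets. It has no linear predictor, so there is no intercept to carry a random effect and no interaction term to test.
- Each participant contributes one event or censoring time. There are no repeated outcomes within a person to correlate.
- By the Recruitment section everyone enters without diabetes. The baseline value is the same for all and has zero variance, so a pre-post correlation is undefined.

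**2. Does the sample size rest on the faulty clause?**

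Inputs from Statistical analysis: 19.8% control, 8.6% intervention, alpha 0.05, power at least 0.80, dropout 25%, N = 420. Assumed because not stated: two-sided test, 1:1 allocation, proportional hazards.

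- Hazard ratio: ln(1 − 0.086) / ln(1 − 0.198) = 0.408.
- Events by Freedman: (1.960 + 0.842)² × (1.408/0.592)² = 44.3, rounded up to 45.
- Average event risk: (0.198 + 0.086)/2 = 0.142. Evaluable: 45/0.142 = 317. Recruited: 317/0.75 = 423, against 420 in the plan.
- Two-proportion formula, pooled: 152 per arm, or 406 after dropout. With the difference rounded to 11 points (19.8% vs 8.8%): 158 per arm, or 422.

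So 420 is consistent with an ordinary log-rank or two-proportion design. Neither includes a random effect.

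**3. Power of a plain log-rank test at N = 420**

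- Evaluable: 420 × 0.75 = 315. Expected events: 315 × 0.142 = 44.7.
- Schoenfeld: Φ(|ln 0.408| × √44.7 / 2 − 1.96) = Φ(1.04) = 0.85.
- Freedman: Φ((0.592/1.408) × √44.7 − 1.96) = Φ(0.86) = 0.80.
- Simulation (2,000 runs, 210 per arm, events detected only at 6, 12, 18 and 22 months, exponential event times, 25% dropout spread over time): power 0.86. Type I error was 0.049 with 14% incidence in both arms.

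**4. What if someone keeps the random intercept and gives up the log-rank test?**

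One such reading is a random-intercept logistic model of diabetes status at the four visits, where status stays positive once reached. It was fitted to the expected pattern frequencies under constant hazards giving 19.8% and 8.6% at 22 months. The likelihood-ratio (LR) statistic is for 157.5 completers per arm.

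| Random-intercept SD | Negative log-likelihood per pair | Treatment odds ratio | log OR / SD | LR statistic for treatment |
|---|---|---|---|---|
| 0.01 | 2.377 | 0.39 | – | 22 |
| 4 | 1.340 | 0.10 | −0.58 | 10.3 |
| 8 | 1.230 | 0.015 | −0.53 | 9.0 |
| 12 | 1.201 | 0.002 | −0.51 | 8.5 |
| 24 | 1.183 | below 0.001 | −0.50 | 8.2 |

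The fit keeps improving as the SD grows. It is still improving at SD 40 (1.180), so there is no interior maximum, and the odds ratio depends on where the software stops. The test behaves differently. Over SD 4 to 24 the LR statistic runs from 10.3 to 8.2 (p about 0.001 to 0.004), near the plain log-rank expectation of (ln 0.408)² × 44.7/4 = 9.0.

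**5. The visit-by-visit fallback**

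Four independent tests at 0.05 would give a family-wise error of 1 − 0.95⁴ = 18.5%. Cumulative incidence is correlated across visits, so this is an upper figure and the true one is lower.

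**The case against.** The strongest reply is that the plan already fixes what matters: the endpoint, the visits, the contrast, intention-to-treat and the name of the test. Strike the surplus clause and a workable log-rank test is left, with the planned sample size intact. That is right, and it limits the point to a faulty description of a sound test.

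It could also be said that a frailty or discrete-time model was meant, or that the analysis plan will settle it. The article names no such model. A frailty for each person with one terminal event is at best weakly identified, through distributional assumptions. As for the analysis plan, the article does not leave the test open. It states one that cannot be carried out, and a later document could only replace it.

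Three stronger readings are tempting and are not supported:

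- **That the main p-value is arbitrary.** The logistic model above is not named in the plan. Even there, only the odds ratio drifts; where the likelihood is heading, the test stays close to the log-rank test.
- **That the test will be chosen after the data are seen.** An analysis plan may exist that names the working test. The article does not show when the choice was or will be made.
- **That the Chi-square or Fisher sentence is a rival primary analysis.** It is general. The sentence introduced specifically for the primary outcome takes precedence.

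**Conclusion.** The point holds as an error in how the primary analysis is stated. The random-intercept clause and the interaction step cannot be part of a log-rank test, and there is no pre-post correlation in a once-only event among people who all start without diabetes. With the visit-by-visit fallback also in place, the article does not pin down a single primary test.

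The size is modest. The sample size of 420 does not change: power with an ordinary log-rank test is about 85% (Schoenfeld) or about 80% (Freedman) with 315 evaluable participants. These figures assume a two-sided test, 1:1 allocation and proportional hazards; the simulation and the logistic illustration also assume constant hazards. Because it concerns the main test and costs almost nothing to correct, it should be corrected before the analysis.

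**What to change.** Rewrite the primary-outcome part of Statistical analysis:

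1. Delete the random-intercept and pre-post clause for the primary outcome. Keep it only for repeated continuous outcomes.
2. Name one primary test: a two-sided log-rank test of time to first diabetes diagnosis in all randomised participants, preferably stratified by the randomisation factors centre and sex.
3. Give an effect estimate with a 95% CI from a model suited to diagnoses found only at 6, 12, 18 and 22 months. A grouped-time proportional-hazards model with a complementary log-log link is one choice; its details can be left to the analysis plan.
4. Remove the time-by-group interaction step and the visit-by-visit comparisons from the primary analysis, or label them secondary.
5. For clarity, add that the Chi-square or Fisher comparison is not the primary test.

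The cost is one paragraph of wording. No new data, visits or participants are needed.

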### Randomization

In this study, a stratified blocked randomization strategy will be used to achieve between-group comparability, and to avoid imbalance in the number of subjects in each stratum. The randomization entails measuring the level of the stratified factors—center and sex—for eligible subjects, determining to which stratum each belongs, and using a block size of 4 within each stratum. Stratified blocked randomization in both centers will be conducted by study staff not involved in the intervention through a central computerized process. The sequence of group allocations will be concealed until after the baseline data collection is completed.

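### A time-by-group interaction pre-test decides whether the primary outcome is judged by one overall comparison or by four visit-wise ones, so the data choose the primary hypothesis

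*Protocol article*

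**What the plan says.** The Statistical analysis section of the Protocol article ties the design to a single comparison: "The C-KDPS sample size was determined for the primary outcome (between-group difference in diabetes incidence) at 22 months’ follow-up". Alpha is set at 0.05 and power at 0.80 or more, and the assumed cumulative incidences are "control group = 19.8% vs. intensive LSI group = 8.6" percent. The total allows for dropout: "A total of 420 subjects should be recruited, considering the dropout rate of 25% during the study period".

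The section then describes a mixed-model analysis of covariance for clinical parameters and, for the primary outcome, a log-rank test on cumulative incidence that is given a random intercept. Immediately after that sentence it says that an interaction between time and intervention group is assessed first, and continues: "If there is no interaction effect, the overall intervention difference will be assessed. Otherwise, the intervention difference will be assessed at each time point".

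The time points come from Study outcomes: "A 75-g OGTT with HbA1c level testing is scheduled at 6, 12, 18, and 22 months".

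The article gives no level for the interaction test, no level or correction for the visit-wise assessments, and no visit that takes priority on that branch.

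**The concern.** The rule is stated, not merely left out. Where it stands, it governs the primary outcome. A preliminary test selects the hypothesis: one overall difference, or one difference per visit in place of it. This has two consequences.

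- **Type I error.** A procedure that chooses between one test and several after looking at the data does not in general keep the 0.05 on which the sample size rests.
- **The primary answer.** If the interaction is flagged, the overall comparison is replaced. The trial then reports up to four results, which may disagree, and the text does not say which of them decides whether diabetes was prevented.

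The second point has some force here because contact is front-loaded (18 sessions in 24 weeks, then less frequent visits), so an effect that changes over time is plausible. A non-significant interaction with about 50 expected events is also weak evidence that the effect is constant.

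**Working it through.** **Inputs from the document.** Alpha 0.05; power at least 0.80; 22-month incidence 19.8% (control) and 8.6% (intervention); N = 420; dropout 25%; visits at 6, 12, 18 and 22 months.

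**Assumptions.** Two-sided alpha; 1:1 allocation (the ratio is not stated, but blocks of 4 are used); constant control hazard; dropout spread evenly over time; interaction test at 0.05 (0.10 as a sensitivity case); visit-wise tests at 0.05.

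**1. Reproducing the plan's N.**
- Hazard ratio = ln(1 - 0.086) / ln(1 - 0.198) = 0.408.
- Freedman events = (1.96 + 0.84)² × [(1 + 0.408) / (1 - 0.408)]², about 45.
- Mean incidence = (0.198 + 0.086) / 2 = 0.142, so 45 / 0.142 = 317 evaluable.
- 317 / 0.75 = 423, against the stated 420.

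The sample size therefore matches one log-rank comparison at 0.05.

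**2. Type I error of the two-stage rule.** Under the null:

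P(reject) ≈ P(no flag) × 0.05 + P(flag) × P(any visit significant | flag).

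This was simulated with 200,000 null trials of 210 per arm, at 22-month incidence 14.2% and 19.8%. The log-rank test was formed over the four visits and the interaction was a 3-df heterogeneity test.

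| Meaning of a visit-wise test | P(any visit significant, given flag) | Approximation with a 5% flag rate | Simulated |
|---|---|---|---|
| Cumulative incidence to that visit | about 0.40 | 0.95 × 0.05 + 0.05 × 0.40 = 0.0675 | about 6.7% |
| Incidence in the interval before that visit | about 0.92 | 0.95 × 0.05 + 0.05 × 0.92 = 0.0935 | 9.0-9.2% |
| Overall log-rank alone, no pre-test | not applicable | not applicable | 5.0% |

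The simulated values sit slightly below the approximation because the heterogeneity test fires in a little under 5% of null trials. The approximate ceiling with a 0.05 pre-test is 0.95 × 0.05 + 0.05 = 0.0975.

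**3. Sensitivity.**
- Pre-test at 0.10: about 7.7-8.1% (cumulative) and 9.5-12.3% (interval), across 3-df and linear 1-df forms of the interaction test.
- Bonferroni at the visits (0.05 / 4 = 0.0125) with a 0.05 pre-test: about 5.6-6.8%. Part of the inflation comes from the pre-test itself.
- Only the 22-month cumulative comparison on the interaction branch: back to about 5.0%.

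**4. Under the planned effect (proportional hazards, ratio 0.408).** The interaction is flagged in about 2% of trials. Power is about 87% for the overall test and about 87% for the two-stage rule. Unconditional visit-wise power at 6, 12, 18 and 22 months is about 40, 66, 81 and 87% for cumulative tests and 40, 36, 33 and 21% for interval tests.

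**5. If the effect changes over time.** These scenarios are illustrative and are not taken from the document.
- Interval hazard ratios 0.25, 0.35, 0.6, 0.8: overall comparison replaced in 13% of trials.
- Interval hazard ratios 0.15, 0.3, 0.8, 1.0: replaced in 38%.
- No effect to 6 months, then the planned 22-month rates: replaced in about 44-61%, depending on the form of the interaction test.

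**The case against.** Four points can fairly be made for the plan.

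- **The text may not mean this.** A standard log-rank test has neither a random intercept nor a time-by-group term. Both belong to the repeated-measures mixed model described just before, so the interaction step may be misplaced text about that model. This stands as a real ambiguity. But the step follows the primary-outcome sentence and nothing restricts it to secondary outcomes, so the text needs correcting on either reading.
- **Silence is not a decision.** A reader might infer four tests each at 0.05 with no correction. The article does not say so, and a condensed article may leave multiplicity to a fuller document. That stands, so the absence of a correction is not the complaint. The branching is stated, and Bonferroni at the visits would neither fully restore 0.05 nor give back one primary answer.
- **The inflation is modest.** A reader might quote 1 - 0.95⁴ = 18.5% for four independent tests. That would apply only if all four were always run. Here the visit-wise branch is reached in about 5% of null trials.
- **Power is not lost.** A reader might infer that a well-powered test gives way to weak ones, citing 40, 36, 33 and 21%. Those figures hold only for interval tests. The primary outcome is framed as cumulative incidence, for which the 22-month comparison keeps about 87%. With the planned effect the switch is rare, and the two-stage rule rejects as often as the overall test.

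**Conclusion.** The concern holds in a moderate form. As written and placed, a data-driven pre-test chooses between one primary comparison and four. With both stages at 0.05, type I error is about 6.7% on the more natural cumulative reading and about 9% on the interval reading, against 5.0% for the log-rank test alone. Power under the planned proportional effect is unaffected.

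The more lasting harm is interpretive. If the effect wanes or builds, the single pre-specified answer may be replaced by several with no stated priority. How often depends on effect patterns that the document does not give, so the 13-38% for waning effects is illustration, not forecast.

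The type I figures rest on assumed test levels, two-sided testing, 1:1 allocation, constant hazard and even dropout. Their direction does not depend on the form of the interaction test that was tried. Severity: should-fix.

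**What to change.** Replace the branching rule with three statements:

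1. The only confirmatory test of the primary outcome is the overall log-rank comparison over 0-22 months at two-sided 0.05, performed and reported whatever the interaction shows.
2. The time-by-group interaction and the visit-specific cumulative incidences, with confidence intervals, are supportive and carry no claim of success.
3. If that was the intent, the interaction step and the random intercept apply to the repeated-measures mixed model for secondary outcomes.

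Naming the 22-month cumulative comparison as the sole test on the interaction branch would also bring type I error back to about 5.0%, but it keeps a step that serves no purpose for the primary outcome.

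The cost is a few sentences, settled before any unblinded analysis. No extra participants, visits or data are needed, and N = 420 stands.

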## Discussion

### Importance of diabetes prevention: To whom and how?

Type 2 diabetes is a serious health concern all over the world. In particular, people originating from South Asia and China develop type 2 diabetes at a higher rate, at an earlier age, and at a lower range of BMI than do their white counterparts [25]. Korea is no exception. The socioeconomic and health costs for diabetes are also enormous in Korea [26]. According to the annual report from the NHIS under the Ministry of Health and Welfare in Korea, diabetes is the sixth leading cause of death in the country and the fourth greatest expense in the health insurance budget [27]. Many countries take preventive measures at the government level. Such measures should be accompanied by an enormous budget, related professional manpower, and effective strategy. Therefore, selection of an appropriate target population and a cost-effective prevention program are needed.

A meta-analysis of RCTs demonstrated that intensive LSIs are highly effective in the Asian population, as elsewhere [28]. A meta-analysis of eight RCTs found a 45% reduction in the incidence of new type 2 diabetes in Asian people assigned to the intervention arm (OR 0.55, 95% CI 0.44–0.70) [29]. Almost all the diabetes prevention studies included subjects with pre-diabetes range. We designed the inclusion criteria for C-KDPS according to ADA criteria, and subjects with an HbA1c level of 5.7–6.4% were included as high-risk individuals.

However, even a perfect diabetes prevention program is of no use if the high-risk individuals are not screened or are inappropriately selected. Community-based screening of type 2 diabetes across the country is realistically impossible without sufficient budget. Therefore, community-based DPS could be tried if the healthcare system is provided by government in real practice. From this perspective, Korea has perfect conditions to perform a diabetes prevention program due to government-supported regular health examination service for all Korean people and public healthcare centers throughout the country. Public healthcare centers located near to the participant’s resident area would be the best places for C-KDPS.

